### Patient recruitment, randomization and procedure of the treatment

Participants are recruited via articles in newspapers, family doctors and gynaecologists, flyers, and different social networks.

Eligible participants undergo four assessments (see Figure 
1). In the first assessment (t0-assessment), participants fill out a retrospective screening of premenstrual symptoms
[50] according to the DSM-5 criteria
[7]. If participants fulfil the basic inclusion criteria and primary DSM-5 criteria (that is, five premenstrual symptoms including at least one affective symptom), a structured clinical interview regarding comorbid disorders is conducted via telephone. Afterwards, principally eligible participants are invited to complete a daily symptom rating during two consecutive menstrual cycles, as requested by the DSM-5 and ACOG criteria. During one of the premenstrual (luteal) phases within these two cycles, the participants fill in the pre-treatment assessment (t1-assessment) including primary (impairment of premenstrual symptoms) and secondary outcome measures (coping with premenstrual symptoms, social support, quality of partnership, level of stress). If the participants fulfil the diagnostic criteria of a severe PMS or PMDD with regard to the daily symptom rating, they are randomly assigned to either the treatment or the wait-list control group. In addition, they are randomized to one of two psychologists who will be the responsible psychologist throughout the study.

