### Sample size and power calculations

Effect sizes of the difference between an iCBT programme for PMS and a wait-list control group cannot be estimated precisely because the combination of these two approaches – CBT and internet-based interventions – for treating PMS has not yet been evaluated systematically.

First, there is currently no internet-based self-help programme for PMS. However, iCBT has been found to be effective for disorders sharing common symptoms with PMDD (for example, affective and somatic disorders)
[39]. Large effects for internet-based treatments with psychologist support for depression and anxiety disorders compared to control conditions were found in a meta-analysis
[49]. The effects found for internet-delivered treatments aimed at health problems (pain and headache) were comparable to the effects for face-to-face interventions
[47].

Second, CBT face-to-face programmes for PMS are not well evaluated and suffer from a limited methodological quality as well
[36, 39]. In one meta-analysis examining CBT for PMS
[36] the authors found medium effect sizes. Small to medium effect sizes were found in another meta-analysis comparing CBT and pharmacological interventions
[40].

By considering the different effect sizes found in the cited studies and the insufficient current state of research, we based our sample size calculation on an expected medium effect size (*f* = 0.25, α = 0.05, power 80%). The validity and retest reliability of two applied tests is evaluated in a pilot study and thus is not known yet. Therefore, we assumed a conservative retest reliability. For a 2 × 2 multivariate analysis of variance (MANOVA) the total sample size is set to *N* = 128.

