In addition to written information and audio files, participants receive email feedback from a psychologist on a weekly basis. The psychologists are Master level clinical psychologists who are at an advanced stage of CBT training. To ensure therapist adherence to the manual they receive regular supervision by a licensed CBT therapist.

The modules and audio files, as well as the secured messaging system to communicate with the clinician, are delivered via a website.

To investigate patient compliance with the treatment, weekly email feedback on the treatment material is required. If participants do not send their feedback they receive two email reminders. If they do not reply to these reminders they are called by their therapist.

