### Statistical analysis

All analyses of the outcomes will be conducted as intention-to-treat analyses. Between-group changes at post-treatment on the impairment and the use of coping strategies will be calculated by using a 2 (pre-treatment/post-treatment) × 2 (experiment group/waiting list) MANOVA. *Post hoc* comparisons will be applied if clarification of the main effects of the MANOVA is needed. Effect sizes between the groups will be calculated with Hedges’ g.

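### The stated 2 × 2 MANOVA leaves out the psychologist, a factor the trial itself randomises, so any difference between the two psychologists goes unexamined (minor)

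*Protocol article*

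**What the plan says.** The protocol article (Patient recruitment, randomization and procedure of the treatment) describes two random allocations. For the first, "they are randomly assigned to either the treatment or the wait-list control group". For the second, "they are randomized to one of two psychologists who will be the responsible psychologist throughout the study". As written, the second applies to all randomised women, so psychologist is crossed with arm.

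Under Intervention, "participants receive email feedback from a psychologist on a weekly basis". The psychologists work to a manual under supervision, and the therapist telephones women who do not answer reminders. Under Assessments, either the interviewer or the therapist may call a woman who has not completed a questionnaire. The wait-list group gets no treatment material during its 8 weeks.

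The Statistical analysis section names the factors of its model for impairment and coping: "2 (pre-treatment/post-treatment) × 2 (experiment group/waiting list) MANOVA". Under Sample size and power calculations, "For a 2 × 2 multivariate analysis of variance (MANOVA) the total sample size is set to *N* = 128", with f = 0.25, α = 0.05 and power 80%. Neither section mentions the psychologist.

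**The concern.** A factor that is randomised normally appears in the model. Here it is also part of the intervention, since the psychologist writes the weekly feedback and chases women who fall silent. Up to the t2 assessment the wait-list has had no treatment material, so differences in how the two psychologists deliver the programme act almost wholly in the treatment arm.

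Under the stated model such a difference is counted as residual variation between women. A reader of the results would not learn whether the programme effect was similar under both psychologists, nor that the estimate is an average over two particular people. The Discussion section hopes for later use in the healthcare system, where others would deliver the programme, so the question is of practical interest.

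**Working it through.** **Inputs.** From the article: N = 128, f = 0.25, α = 0.05, two arms, two psychologists. Assumed: 1:1 allocation to arm and to psychologist, because no ratio is stated. This gives 64 women per arm and 128/4 = 32 per arm-by-psychologist cell. Outcomes are in SD units, without baseline adjustment, because the article gives no figure for the retest correlation ("Therefore, we assumed a conservative retest reliability").

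**1. The plan's own figure.** For two groups, f = 0.25 corresponds to d = 0.5. The noncentrality is λ = f²N = 0.0625 × 128 = 8. The F test with 1 and 126 df has power 0.8015; at N = 126 the power is 0.7952. So N = 128 is reproduced with arm as the only between-subject factor.

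**2. Cost of adding the factor.** With psychologist and arm × psychologist as fixed terms there are four cells, and the residual df fall from 126 to 124. With λ still 8, power is 0.8014 and the N needed stays 128.

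**3. What omission costs in precision.** Suppose the psychologists differ by 0.5 SD within the treatment arm and not at all in the wait-list.
- Extra variance in the treatment arm: (0.5/2)² = 0.0625.
- Pooled over two equal arms: 0.0625/2 = 0.031.
- Standard error ratio: √1.031 = 1.015, an increase of about 1.5%.

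A psychologist main effect alone would remove half of that extra variance: averaged over arms, the psychologists deviate by ±0.125 SD, and 0.125² = 0.0156. The main effect and the interaction with arm together remove all of it.

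**4. What can be learned about each psychologist.**

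| Contrast | Standard error (SD units) | 95% CI half-width or power |
|---|---|---|
| One psychologist's own arm effect (32 vs 32) | √(2/32) = 0.25 | 1.96 × 0.25 = ±0.49 |
| Difference between the two arm effects | √(4/32) = 0.354 | 1.96 × 0.354 = ±0.69; power 0.29 for a true difference of 0.5 SD, 0.80 for 1.0 SD |
| Psychologists compared within the treatment arm at t2 (32 vs 32) | 0.25 | power 0.12 at d = 0.2, 0.50 at d = 0.5, about 0.80 at d = 0.71 |

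The contrasts can be estimated, but only roughly.

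**The case against.** **The omission does little harm to the planned comparison.** This stands. Psychologist is randomised, so the arm contrast is unbiased for these two psychologists. Leaving the difference in the error term is slightly conservative, and step 3 puts the loss at about 1.5% of the standard error even for a sizeable difference. The manual and supervision may make the real difference smaller.

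**A condensed article leaves such detail to an analysis plan.** This stands in part. An unseen plan may contain the term, which lowers the weight of the point. But the article lists the factors of the model, and a factor the trial randomises is not in the list.

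**Two stronger readings are tempting, and the documents support neither.**

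- A reader might infer that a psychologist effect cannot be told apart from a programme effect. The allocation to psychologist is random, so the two can be compared within the treatment arm at t2 and within the wait-list after its own treatment at t3. What the design cannot separate is the psychologists' shared contribution from that of the written modules, because feedback is part of the programme and the control is a wait-list. A psychologist term would not change that.
- A reader might infer that the type I error is inflated. That holds only if the result is claimed for a wider population of psychologists. The Statistical analysis section makes no such claim, and the article gives no psychologist intraclass correlation. On assumed values of 0, 0.01, 0.05 and 0.10, using a design effect of 1 + 31 × ICC in the treatment arm, a nominal 5% test would run at 5.0%, 6.8%, 14.1% and 22.0% for that wider claim. A fixed factor does not repair this, and two psychologists are too few to estimate a variance component. These figures are therefore no argument for the fix; they only show why the scope of inference should be stated.

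**Conclusion.** The point holds as a minor one. The stated model omits a randomised factor that is part of the intervention. As a result, any difference between the two psychologists sits in the error term and is not looked at, and the result is conditional on these two without the article saying so. There is no bias in the arm comparison for these psychologists, and the effect on power is negligible (0.8014 with the factor and its interaction, 0.8015 without). The gain from correcting it is chiefly in description and in a clear scope of inference. The figures assume 1:1 allocation to arm and to psychologist, and outcomes in SD units without baseline adjustment.

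**What to change.** Add psychologist, as randomised and in both arms, as a fixed between-subject factor in the primary model. As a descriptive check only, report the arm × psychologist contrast and each psychologist's own arm effect with its 95% CI. With the precision shown above, a non-significant interaction must not be read as evidence that the psychologists are alike. State in one sentence that inference is to these two psychologists.

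The cost is 1 degree of freedom for the factor, or 2 with the interaction. It needs no extra participants and no new data, because the psychologist is assigned at randomisation. If the analysis plan already has the term, it is enough to make the article's description agree with it.

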**Figure 1 Fig1:**
[figure not shown]
**Study process.** t = measurement points: t0 = screening for basic inclusion criteria. t1 = first assessment of primary and secondary outcome in luteal phase, first and second cycle of the symptom diary. t2 = second assessment in luteal phase, third and fourth cycle of the symptom diary, approximately 2 months after admission. t3 = for the wait-list group only, third assessment of primary and secondary outcome in luteal phase, fifth and sixth cycle of the symptom diary, approximately 6 months after admission. t4 = for the treatment group: third assessment of primary and secondary outcome in luteal phase, approximately 10 months after admission; for the wait-list group: fourth assessment of primary and secondary outcome in luteal phase, approximately 14 months after admission.

Participants randomized to the treatment group receive the *Praemensis* Programme, a CBT-oriented self-help treatment lasting 8 weeks. After completion of the treatment, participants complete the daily symptom rating and the questionnaires during the luteal phase (t2-assessment).

Participants assigned to the wait-list have to wait for 8 weeks and do not receive any treatment material. After the waiting period they complete the symptom diary and the questionnaires during their luteal phase (t2-assessment). Subsequently they receive the same treatment and the same post-assessment (t3-assessment). Six months after the end of the treatment the follow-up t4-assessment is administered in the luteal phase. It consists of the same questionnaires as administered at t1, t2 and t3.

### Intervention

The treatment *Praemensis* Programme is based on CBT principles. The treatment lasts 8 weeks and its ingredients are distributed across 14 separate chapters, called modules. Before starting the treatment, participants receive detailed instructions on how to use the information, how every module is structured, on the importance of exercises and on how to deal with technical obstacles.

The treatment starts with an introduction module and ends with a module about relapse-prevention. The modules in between are divided into two arms: cognitive strategies and suggestions for behavioural changes in lifestyle. For an overview see Table 
1. Consequently, except for the first and the last week, participants work on two modules in parallel. For these modules, an approximate working time of 5 hours per week is suggested.

**Table 1 Tab1:** **Content of the different modules**

Week	Content of the module	
	Cognitive strategies	Behavioural changes in lifestyle
1	**Module 1:** Psychoeducation about PMS/PMDD and its aetiology	
2	**Module C1:** Psychoeducation about the role of thoughts and the relationship to feelings and behaviour (cognitive triad)	**Module B1:** Psychoeducation about the interrelation between stress and PMS and learning of relaxation techniques
3	**Module C2:** Transfer to PMS-specific context	**Module B2:** Psychoeducation about the interdependency between alimentation, sport and PMS
4	**Module C3:** Restructuring of dysfunctional cognitions	**Module B3:** Integration of sports into daily life by motivational plans and strategies
5	**Module C4:** Psychoeducation about PMS-specific myths and application of learned cognitive strategies	**Module B4:** Balanced diet and implementation into daily life
6	**Module C5:** Psychoeducation about helpful thoughts and development of new appraisals	**Module B5:** Psychoeducation about the influence of stress-related errors in reasoning
7	**Module C6:** PMS-specific behaviour (healthcare utilisation, protection, communication)	**Module B6:** Training of consumption and implementation of positive activities into daily life
8	**Module 8:** Review of the training and relapse-prevention	

PMDD, premenstrual dysphoric disorder; PMS, premenstrual syndrome.

The first module includes psychoeducation about PMS/PMDD, its aetiology, and treatment. The cognitive modules provide information about, and strategies for, identifying and modifying dysfunctional cognitions – especially PMS-specific cognitions – and PMS-specific myths and behaviours. The modules including suggestions for lifestyle changes cover topics such as stress reduction, sports, and balanced diet. In the last module, a summary as well as a plan to maintain gains and prevent relapse is provided. All modules are available for download in pdf format. They all include practical exercises for applying and practicing the provided theoretical contents. Additional audio files are provided in order to facilitate conducting these exercises, such as a tutorial about progressive muscle relaxation or an audio instruction for an exercise to collect PMS-associated thoughts.

In addition to written information and audio files, participants receive email feedback from a psychologist on a weekly basis. The psychologists are Master level clinical psychologists who are at an advanced stage of CBT training. To ensure therapist adherence to the manual they receive regular supervision by a licensed CBT therapist.

The modules and audio files, as well as the secured messaging system to communicate with the clinician, are delivered via a website.

To investigate patient compliance with the treatment, weekly email feedback on the treatment material is required. If participants do not send their feedback they receive two email reminders. If they do not reply to these reminders they are called by their therapist.

### Assessments

Clinical primary and secondary outcomes will be assessed by both self-report questionnaires and clinical interviews. To ensure compliance with the assessment, participants receive two reminders via email for every questionnaire they do not complete. If they do not reply, the interviewer or the therapist calls the participant.

#### Diagnostic assessment

Premenstrual symptoms are assessed with two instruments (screening and diary). The German DSM-IV-TR-based Questionnaire for the Screening of Premenstrual Symptoms was used for the screening as well as for the self-development of the diary
[50]. It measures the different dimensions of the premenstrual symptoms in a very detailed way. The questionnaire consists of 27 items which cover the diagnostic criteria of the DSM-IV-TR and which is adapted according to the DSM-5. Three additional items measure the impairment caused by the checked symptoms (for example, "My social activities are impaired by these symptoms"). All 30 items are rated on a four-point rating scale ranging from 0 (not true at all) to 3 (absolutely true).

These 30 items are assessed first in the retrospective screening (t0). Here, the items are answered for the luteal and the follicular phase separately. Second, in the prospective diary, participants rate the 30 items on a daily basis. A total score as well as a distress index are calculated. The distress index reflects the intensity of the symptoms calculated averaged across 5 days.

#### Demographic variables

The following demographic variables are measured at t0: age, family status, sexual orientation, citizenship, country of birth, growing up country (of the participant, her mother and her father), religion, mother tongue, highest degree, employment status, height, weight, and number of births and aborts.

#### Primary outcome

**Impairment caused by premenstrual symptoms** The impairment caused by the premenstrual symptoms is measured with a self-developed questionnaire called the Premenstrual Syndrome Impairment Measure (PMS-B), based on the German Pain Coping Questionnaire
[51], the Pain Disability Index
[52] and the Self-Report Measure for the Assessment of Emotion Regulation Skills
[53]. It is currently being validated in a pilot study. It consists of two subscales (mental and functional impairment), with seven items for each. The five-point Likert scale ranges from 0 (not true at all) to 4 (absolutely true). Mean values for the subscales as well as for the whole test are calculated.

#### Secondary outcome

**Coping with premenstrual symptoms** Coping with premenstrual symptoms is assessed by a self-developed questionnaire, the Premenstrual Syndrome Coping Measure (PMS-C). It is based on the German Pain Coping Questionnaire
[51], the German Version of the Coping Strategies Questionnaire
[54], the Self-Report Measure for the Assessment of Emotion Regulation Skills
[53], and the Brief COPE
[55]. It consists of five scales with four items each, which are replied to on a five-point scale ranging from 0 (not true at all) to 4 (absolutely true). Mean values are calculated for the subscales as well as for the total scale. This questionnaire is also being validated in a pilot study.

**Social support** The Short-Form Social Support Questionnaire
[56] is employed to measure the availability of social support. This 22-item measure consists of three subscales: emotional support, practical support, and social integration. Four additional items measure satisfaction with the social support and availability of a person of trust. Each item is rated on a five-point scale ranging from 1 (not true at all) to 5 (absolutely true). A mean value for the whole scale is calculated
[57]. A moderate to high reliability has been found in different studies
[57, 58]. A good to very good factorial validity has been demonstrated
[57].

**Quality of partnership** The quality of partnership is measured with a 25-item measure, the Questionnaire for the Assessment of Relationship Quality
[59]. It consists of six scales: fascination (three items), engagement for the relationship (five items), sexuality in the relationship (five items), perspective of the relationship regarding the future (five items), mistrust to the partner (three items), and restriction of the independency (five items). The single subscales as well as the total score can be interpreted. Good psychometric properties have been shown with Cronbach’s alpha for the subscales ranging between 0.75 and 0.94
[59]. Good to very good convergent validity was demonstrated (r = 0.59 to 0.84) by two questionnaires measuring partnership quality and partnership satisfaction and a further questionnaire measuring depressive mood
[59].

**Level of stress** The Perceived Stress Scale is used to assess the appraisal of situations in life as stressful, particularly as "unpredictable, uncontrollable, and overloaded"
[60]. It consists of ten items forming the aggregate value. The items are rated on a five-point scale from 0 (never) to 4 (very often). Good reliability (α = 0.89) as well as good convergence (r = 0.73) with the State-Trait Anxiety Inventory and good divergent validity (r = 0.02 to 0.18), for example with the Sensation Seeking Scale, are supported in a recent study
[61].

### Statistical analysis

All analyses of the outcomes will be conducted as intention-to-treat analyses. Between-group changes at post-treatment on the impairment and the use of coping strategies will be calculated by using a 2 (pre-treatment/post-treatment) × 2 (experiment group/waiting list) MANOVA. *Post hoc* comparisons will be applied if clarification of the main effects of the MANOVA is needed. Effect sizes between the groups will be calculated with Hedges’ g.

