[14]. Regardless, the use of a new combined pill including progestin which has not been derived from testosterone (Yasmin®, Bayer Health Care, Leverkusen, Germany) is promising and its application is thus recommended by the RCOG
[17].

Furthermore, selective serotonin re-uptake inhibitors (SSRIs) are recommended as one of the first-line pharmacological management options
[17]. Four meta-analyses support the efficacy of SSRIs
[30–33]. However, side effects of SSRI treatment
[30, 34] lead to high rates of withdrawal from treatment. Further problems are the high placebo reaction in patients suffering from PMS
[35] and the low responder rate of 40%
[32].

Because of the problems of pharmacotherapy, CBT has been suggested as an additional treatment approach
[36, 37] and has even been named a routine treatment option in the guidelines of the RCOG
[17]. Theoretical substantiation for the adoption of CBT for PMS/PMDD comes from the cognitive model for PMS by Blake and colleagues
[38]. The model emphasizes the importance of cognitive appraisal of the premenstrual symptoms and the associated distress. Here, CBT can intervene by questioning the attributions and by teaching coping skills. In addition, CBT has been shown to be effective for disorders sharing common symptoms with PMS/PMDD (for example, affective and somatic symptom disorder)
[39]. Some studies showed promising results for CBT interventions for PMS/PMDD. In a meta-analysis examining CBT for PMS, nine studies were included
[36]. The authors found medium effect sizes for reducing anxiety and depression. Another meta-analysis, containing 22 studies, revealed small to medium effects for CBT and serotonergic antidepressants concerning different outcomes (for example, mood and functional impairment)
[40]. To date, only a small number of well designed RCTs have investigated the efficacy of CBT for PMS
[36, 39]. Methodological limitations are, for instance, a lack of description of the randomization and treatment procedure, substantial loss to follow-up, and potential reporting bias. Besides, they show partially contradicting findings with unsatisfactory
[40] or lacking evidence
[39] contrasting findings of significant improvement
[36]. Thus, one aim of the current study is to develop a well-designed, CBT-oriented self-help programme and to examine its efficacy for distress reduction in PMS patients.

The high percentage of women being dissatisfied with their actual treatment

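### The pre/post MANOVA named for the main analysis does not by itself deliver the promised intention-to-treat analysis when post-treatment (t2) scores are missing

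*Protocol article*

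**What the plan says.** All references are to the Protocol article.

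- **Population** (Statistical analysis): "All analyses of the outcomes will be conducted as intention-to-treat analyses".
- **Method** (same section): between-group changes in impairment and coping "will be calculated by using a 2 (pre-treatment/post-treatment) × 2 (experiment group/waiting list) MANOVA". No rule is given for a randomised woman whose post-treatment scores are missing.
- **Timing** (Patient recruitment, randomization and procedure of the treatment): t1 is completed during the diary cycles. Only women whose diaries then confirm the diagnosis are randomised: "they are randomly assigned to either the treatment or the wait-list control group". Treated women complete t2 once the treatment is finished, and wait-list women once the waiting period is over.
- **Retention** (Assessments): each uncompleted questionnaire triggers two email reminders and then a call.
- **Sample size** (Sample size and power calculations): "the total sample size is set to *N* = 128", for f = 0.25, α = 0.05 and 80% power. No allowance for dropout is stated.
- **Earlier trials** (Background): their listed weaknesses include "substantial loss to follow-up, and potential reporting bias". No rate is quoted.

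**The concern.** An intention-to-treat analysis keeps every randomised woman in her assigned arm. A standard repeated-measures MANOVA can use only women with a full set of scores. The article chooses the second to carry out the first, so the population actually analysed depends on a step that is not described.

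Two things are at stake.

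1. **Comparability of the arms.** If the women without t2 differ between arms, the women left in the analysis no longer form a randomised comparison. Unequal loss is conceivable here. The treated arm is asked for about 5 hours of work a week with weekly feedback, while the wait-list arm receives its treatment only after t2.
2. **The primary outcome depends on a secondary one.** If PMS-B and PMS-C enter one multivariate test, a woman who returned PMS-B but not PMS-C loses her observed primary outcome as well.

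**Working it through.** **1. Which scores are exposed.** The change contrast for PMS-B needs t1 and t2. A joint test of PMS-B and PMS-C needs four scores per woman. Because t1 is collected before randomisation, a randomised woman without t1 should be rare. The realistic exposure is t2, plus PMS-C at t2 if the test is joint.

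**2. The plan's own sample size.** Inputs are f = 0.25, α = 0.05 and N = 128. Equal allocation is assumed, since no ratio is stated. For a 1-df F test, λ = N·f² = 128 × 0.0625 = 8 with 126 denominator df, and power is 0.801. The smallest even N that reaches 80% is 128. The stated figure therefore reproduces exactly on this formula, with nothing added for loss.

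**3. Power if women without t2 are dropped** (same formula; loss rates are assumptions):

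| Loss of t2 | Women left | Power | N needed to keep 128, 128/(1 − loss) |
|---|---|---|---|
| 0% | 128 | 0.801 | 128 |
| 10% | 115 | 0.757 | 143 |
| 20% | 102 | 0.706 | 160 |
| 30% | 89 | 0.645 | 183 |

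This cost depends on the formula. With a repeated-measures interaction, λ = 2·N·f²/(1 − ρ). Even at ρ = 0, power is 0.978 with 128 women and 0.910 with 89. The article says "Therefore, we assumed a conservative retest reliability" but gives no value, so the power cost cannot be pinned down.

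**4. Illustration of bias** (all inputs assumed). Let the effect in all randomised women be 0.50 SD, and let a fraction p of treated women have no t2 and no benefit. If the remaining treated women benefit by b, then (1 − p)·b + p·0 = 0.50, so b = 0.50/(1 − p):

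- p = 0.10: 0.50/0.90 = 0.556, inflated by 11%
- p = 0.20: 0.50/0.80 = 0.625, inflated by 25%
- p = 0.30: 0.50/0.70 = 0.714, inflated by 43%

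**5. Does a mixed model remove this?** No. With only two time points, a woman without t2 contributes only her t1 score. If dropout is unrelated to t1, the model's group difference at t2 is in effect the baseline-adjusted difference among women with t2. Its expected value is again 0.50/(1 − p). A jump-to-reference imputation gives treated women without t2 the wait-list mean, and so returns (1 − p)·b + p·0 = 0.50.

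**6. What the mixed model does gain.** Suppose missing t2 depends on t1 and arm, and the women left differ between arms by Δ SD at t1. With equal SDs and retest correlation ρ, the change-score contrast shifts by −(1 − ρ)·Δ. A model that conditions on t1 does not have this shift. It also adjusts for baseline and keeps PMS-B when PMS-C is missing.

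**The case against.** The strongest objection is that the article nowhere limits the analysis to women with complete data. It states the opposite population. Imputing t2 and then running the MANOVA would include every randomised woman, and a condensed article may leave an imputation rule to a full protocol or SAP that is not shown. This stands against a reader's likely inference that the plan specifies a completer analysis. It does not remove the narrower point: the article itself fixes a method that, on observed data, does not yield the population it promises.

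Three further inferences are tempting but unsupported.

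- **That missing t1 scores matter.** They precede randomisation.
- **That the result will be biased in favour of treatment.** The documents give no dropout rate and no direction. Workload might drive treated women away, but weekly psychologist contact and calls when feedback stops might retain them. The Background remark concerns earlier trials.
- **That the 11% to 43% inflation justifies replacing the MANOVA.** Step 5 of the working shows that the mixed model shares it.

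It is also fair to say that reminders and calls already apply to each missing questionnaire and are not limited to women who finish the modules. These reduce the loss. They do not say how the remaining loss is analysed. Because treated women's t2 is described as following completion of the programme, it is also left open whether women who stop early are assessed.

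The point about PMS-C assumes a joint test and a woman who returns one questionnaire but not the other.

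**Conclusion.** The concern holds in a limited form. The named MANOVA does not by itself deliver the promised intention-to-treat analysis. On observed data it loses every randomised woman without t2 and, if the two outcomes are tested jointly, those missing only PMS-C at t2.

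The size cannot be determined from the documents. The effect inflation of 11% to 43% rests on assumed treated loss of 10% to 30% and on no benefit in every such woman. The fall in power to between 0.757 and 0.645 rests on assumed loss at the same rates and on the 1-df formula, and is small under a repeated-measures interaction formula. Neither range is a forecast.

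This should be fixed, because the analysis of the primary outcome is affected and the remedy is cheap. It is not a must-fix, because the stated intention is right and follow-up of missing questionnaires is already planned.

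**What to change.** 1. Analyse PMS-B total, the primary outcome, on its own in all randomised women. Use a likelihood-based linear mixed model with t1 and t2, t1 means constrained equal across arms, and the group difference at t2 as the estimate. Analyse PMS-C in a separate model.
2. State that t2 is sought from every randomised woman whether or not she completes the modules, using the reminders and calls already planned.
3. Add one control-based (jump-to-reference) sensitivity analysis for treated women without t2. The mixed model assumes that t2 is missing at random, so only this analysis addresses the possibility that treated women without t2 had no benefit.

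The cost is a change of analysis wording and a little more programming, and the estimate may be less favourable. The Trial status section says recruitment was still ongoing, so the statement on t2 could still take effect for women who have not yet reached that assessment.
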